## Objectives

The primary objective of The Perinatal Bereavement Project is to assess the effects of international bereavement guidelines adapted to the Brazilian context in the mental health and grief experience of mothers who have undergone a perinatal loss. The secondary objective is to verify the prevalence of postpartum depression, anxiety, stress and grief adaptation symptoms, as well as assess the care received in two different moments: before and after the health care professionals are trained and maternity wards are prepared.

## Methods

### Study design

This is a quasi-experimental study that uses qualitative and quantitative methods. It also uses a before-and-after analytical approach.

### Setting

#### Data collection procedures

##### Study phases:

Preparation: This is the phase where the meetings with the maternity ward staff will take place and the Reference Professionals for each maternity will be assigned. Reference Professionals will be responsible for keeping in touch with the researchers who will answer any questions about the project; for organizing training/courses; informing the list of stillbirth and neonatal death cases; etc. They are also going to recommend a Bereavement Professional for the maternity ward. The Bereavement Professional is responsible for bereavement issues regarding the families and the staff. The same person may be both the Reference Professional and the Bereavement Professional. Reference Professionals may be any professional who works at the maternity ward, and has significant experience with the maternity ward routine and procedures, and with the staff. There could be two, both responsible for managing, professional training and guiding. They will be in contact with the family when the allocated professional is absent or ask for guidance. They should be a physician, a nurse or a midwife.

The Bereavement Professional should have experience and skills to offer emotional and technical support to the staff. They may be available to support the families as well. Accordingly, the maternity ward managers may decide if one or two Bereavement Professionals will suffice. Ideally, a psychologist should be the Bereavement Professional, but professionals with further skills may assume the position. The Bereavement Professional will be trained in theoretical and practical contents to offer assistance as required.

The time has come to promote awareness for managers, Bereavement and Reference Professionals regarding perinatal mourning processes. It is also time to elaborate what in Brazil is called Standardized Operational Procedure (SOP) (in Portuguese, “*Procedimento Operacional Padrão*”—POP), and professional qualification.

### Pre-intervention

This phase will consist of two actions: (a) meetings with the focus group and (b) interviews with the women.*The pre-intervention focus group*During the pre-intervention focus group, an informed consent form will be signed, and participants will answer sociodemographic and work experience questionnaires. The meeting will last no longer than 1h30min.*The pre-intervention interview with women*

The pre-intervention interview with the women will be carried out by one of the researchers, based on the stillbirth and neonatal death list provided by the Reference Professional from the maternities ward. They will get in touch to schedule an in-person interview in a place to be defined. Information to verify inclusion and exclusion criteria will be covered. After inclusion criteria are met, the women will receive information concerning the study and will be invited to participate. If they accept, the in-person interview will be scheduled. During this meeting, the informed consent form will be signed. Afterwards, mental health scales will be applied. A qualitative interview will cover socioeconomic, demographic and behavioral data regarding the loss the woman went through.

### Intervention

The intervention will be based on two publications: the Brazilian book “*Como lidar—luto perinatal: acolhimento em situações de perda gestacional e neonatal”* [17], based on the Canadian “Guidelines for health care professionals experiencing a perinatal loss” [15] and the manual provided by SANDS (Stillbirth & Neonatal Death Charity) “Pregnancy loss and the death of a baby: Guidelines for professionals” [14]. Both offer a framework to coordinate important actions to assist families as shown in Fig. 2.

**Fig. 2 Fig2:**
[figure not shown]
A proposal for supportive guidelines regarding stillbirth and neonatal death

Additional material will be published during the investigation and produced along the process. Based on the British manual aforementioned, the initial content will be broadened. This material will be available on www.saude.fmrp.usp.br/lutoperinatal. All documents staff should use during hospitalization (Perinatal loss and Memory creation files) will also be available on the same site. The perinatal loss file will hold relevant information about women’s health and the guideline step-by-step. It will help professionals share information. The memory creating file will provide guidance about the steps taken regarding the baby memory box. A summary of the main actions regarding the supportive guidelines is available on Table 1.

**Table 1 Tab1:** Summary of the main actions on supportive guidelines for families experiencing stillbirth and neonatal death

Summary of supportive guidelines regarding perinatal bereavement	
How to prepare the family to see the baby:	Clean the baby (do not bathe him/her); Dress the baby with diapers, socks, hat, clothes, blanket etc.; Follow the same maternity ward protocol to bring alive babies to see their mothers; Call the baby by his/her name; Follow them up but keep some distance. Never let them unassisted
What should be provided for the memory box:	Hair lock; Handprint and footprint; Placenta stamp (optional); Baby’s pictures; Baby’s first clothes; Baby’s bracelet/identification tag; Cards and letters written by the staff; Leaflets about the bereavement process and bereavement support groups
Which written guidance should be provided:	All information about funeral services and local civil registry office; Information about how to deal with breast milk production; Suppressing lactation Breast milk donation Post-discharge care; Medical appointments and additional exams for further investigation (if necessary); Bereavement support group; Psychological services
What to do to provide continuous care:	Discuss family planning; Schedule regular appointments to assess mental and physical health, and discuss new findings about what happened to the baby (when applicable); In the case of a new gestation, follow health care guidelines for pregnant women who had previously experienced the loss of a baby; Arrange to assist woman during the new puerperium
Guidelines for assisting pregnant women who had previously experienced the loss of a baby:	Remember: this is no longer an ordinary pregnancy, and may be considered a risk pregnancy from the mental health point of view; The previous loss may impact the following bereaved mother’s gestation, from antenatal care through puerperium and breastfeeding; Fear and complaints are expected responses and must be acknowledged; Some parents may prefer to be cared for in a different hospital or by different staff members, which should not be a problem; Mental health screening should be available for both parents; Specialized mental health support or psychological appointments should be encouraged at any time during pregnancy and postpartum; Consider avoiding standard antenatal classes, prioritizing individual preparation sessions for labor, birth and caring for a newborn baby; A special sticker can be used on both notice board and at room’s door wherein a bereaved mother is in labor, so that the staff is aware of her condition; Encourage the writing of a birth plan, so that parents’ preferences can be easily shared with all staff during labor, birth and postpartum Consider scheduling extra and longer antenatal appointments. Extra screening options should be considered whenever necessary or demanded; Set aside a weekly day or time at your institution for pregnant women who had previous perinatal losses to seek assistance if they have questions about their baby's well-being or their pregnancies´ normality; A C-section without clinical recommendation may be considered, when fear from natural birth could not be dealt with after several psychological and communication interventions, as long as the women acknowledge associated risks
What to do when there is: *Stillbirth* *Neonatal death or imminent neonatal death* *Severe malformation (incompatible with life or high death probability)*	1. Assure the mother/family privacy; 2. Deliver bad news properly; 3. Give the family all requested and necessary information; 4. Encourage the preparation of a Care Plan for the women and the baby. This Care Plan includes a birth plan, whenever possible, and a palliative care for the baby, whenever necessary; 5. Choose and prepare a private room, to avoid contact with other mothers and their babies; 6. Apply special stickers on both notice board and at the bereaved mothers’ room door, so that the staff is aware of her condition; 7. Avoid sedation; 8. Respect initial plans – whenever possible; 9. Encourage the mother/family to see the baby; 10. Encourage the mother/family to touch the baby, and to spend time with her/him; 11. Provide the memory box

Regarding the model Training of Trainers, an expert teaches a professional who works in a health care establishment. The one who receives the instructions will teach the others. Therefore, after the implementation of the Project, the qualified professional will continue providing refreshment courses to those who need it. For this specific project, the expert will be the researcher. Another professional will participate in the qualification process and will be in charge of the regional staff after the expert finalizes the project.

The training method consists of the following events:•Perinatal Bereavement Event—training: An in-person event that will be organized with the Regional Health Department XIII. Although it will be focused on specific professionals, managers and Reference Professionals, it will be open to all local professionals. Estimated duration: 3 h.•Reference Professional Meeting: This in-person event aims to prepare and help the Reference Professionals get ready to start the project and write the Standard Operational Procedure (SOP). They will also plan the qualification of the professionals in their health care establishments. Participants: professionals indicated by maternity ward managers (physicians, nurses and psychologists). Estimated duration: 3 h.•Bereavement Professional Meeting: An in-person event aiming to offer the Bereavement Professionals theoretical content about bereavement, the family’s and professional’s points of view, so they may carry out their functions. Participants: professionals indicated by maternity ward managers (physicians, nurses, psychologists and social work professionals). Estimated duration: 4 h.•Coordination meeting: An in-person meeting will be held in each maternity before the staffs are formed. It aims to raise professionals’ and team work awareness on the subject. A video will be produced and will be available to the professionals who could not be present.•Support network to answer any questions and guide professionals involved: During the whole time the project is being carried out, the researchers and the health regional representative can be reached by phone, WhatsApp (general group chat, maternity ward group chats and private messages);•In-person and virtual follow-up will be provided until the end of the project.

Among the actions in accordance with the training methodology, some items will be given to the families. Additionally, the following are to be given to the staff: A box to keep the memories, a polaroid camera and polaroid paper, card for handprints and footprints, a small plastic bag to keep the hair lock, a big plastic bag to keep baby’s clothing items, a blanket that is used when the baby is too small for conventional clothes.

### Post-intervention

This phase consists of two actions: interviews with each woman in the post-intervention group and meetings with the post-intervention focus groups.

One focus group consists of the nurses in each maternity ward and the other is formed by the managers. The interviews and the meeting will mirror the steps taken in the pre-intervention phase.

## Study participants

### Participants

Women who experienced stillbirth and neonatal death in one of the four public maternity wards in Ribeirão Preto City, in São Paulo State, southeast region of Brazil. Health care professionals, employees and managers of the respective maternity wards will also participate.

#### a) Participants and eligibility criteria

All four public maternity wards in Ribeirão Preto were invited to participate in this project and all of them accepted.

No exclusion criteria were outlined for health care professionals, employees and managers.

The *inclusion criteria* for women are:To live in one of the municipalities of the Ribeirão Preto region (XIII Regional Health Department, São Paulo State)Have experienced a stillbirth or a perinatal death during the estimated period^1^;Have faced the death of her baby in the following circumstances:Pregnancy that lasted more than 20 complete weeks;Had a baby weighing at least 500 g;Had a baby that died no later than twenty-eight days after the birth (neonatal death).

Women *exclusion criteria* are to not understand Portuguese and have severe mental health impairment.

The main difference between the pre- and post-intervention groups is the training process health care professionals will receive, together with preparing the maternity ward to implement local protocol. It is estimated that women who had a baby born in the pre-intervention group did not receive a care based on the supportive guidelines regarding perinatal bereavement.

The first 20 women from each group who accept to take part in this study will be interviewed.

#### B) Research instruments and data sources

Data will be collected from women interviewed and from the focus group offered to professionals. We will use a questionnaire specially designed for this project, as well as validated tools used in previous mental health and bereavement studies. Pilot interviews were performed as a way to validate the questionnaire and organize the interview process.

Three scales, that were adapted and validated to Brazilian Portuguese, will be applied:*Perinatal Grief Scale (PGS)*The PGS presents 33 self-applicable psychometric assertions, divided into three subscales, related to perinatal grief adaptation symptomatology. Involves a five-point Likert Scale ranging from “strongly disagree” to “strongly agree”. The cut-off score that we will use is 90, as validated by Paris et al. [34, 35] for the Brazilian population.*Edinburgh Postpartum Depression Scale (EPDS)*The EPDS is a set of 10 self-applicable screening questions, each of them with four multiple choice responses, which indicates the intensity of depressive signs and symptoms that are present during the last seven days before the application. The cut-off score that suggests the woman is probably depressed (or with depression symptoms) is ≥ 11, as validated by Santos for the Brazilian population [35].*Depression Anxiety Stress Scale-21* (DASS-21)DASS-21 is a self-applicable scale with seven items each. It assesses depression, stress and anxiety, considering the previous week. The answers are given in a four-point Likert Scale that vary from 0 (totally disagree) to 3 (totally agree). Score variations correspond to symptom levels such as “normal” and “severe”. The global scores for the three constructs (depression, stress and anxiety) will be calculated as validated by Vignola et al. for the Brazilian population [36].

A sociodemographic questionnaire designed to collect personal data, behavioral information, medical history and information about care received will also be applied.

Each maternity ward will assign the *Reference Professionals* and the *Bereavement Professionals* among their employees.

Data will be provided by each health care establishment. They will send a list containing the stillbirth and neonatal death list, provided by the respective Reference Professionals. The researcher will contact each candidate to verify eligibility for this study, inviting them to participate and scheduling a meeting.

Focus groups will be conducted by the researchers, and the health care professionals who will participate will be contacted by the Reference Professional of each maternity ward.

## Primary and secondary outcomes

### Primary outcomes

A composite of a grief state (grief adaptation symptoms) and rates of depression, stress and anxiety.

### Secondary outcomes

Absence from work due to bereavementPsychiatric treatment due to bereavementMaternal admission to psychiatric health facilitiesSuicide attemptSuicide

### Variables

#### Variables of interest (***Table ******2***)

**Table 2 Tab2:** Variables of interest

	Variables of interest	Data source	Statistical methods
Sociodemographic data:	Age; Marital Status; Schooling; Socioeconomic status; Skin color; Job; Religion	Questionnaire	Descriptive analysis Frequency analysis
Characteristics/ Personal and behavioral information	Recreational activities (sports and artistic activities); Practices sports; Uses drugs (alcohol, cigarettes and/or illegal drugs; Is under medication and/or psychiatric treatment; Participates in religious groups; Undergoes psychotherapy; Participates in bereavement support groups	Questionnaire	Descriptive analysis Frequency analysis
Health history	Gestational age; Miscarriage, abortion, stillbirth or neonatal previous deaths; Illnesses before gestation; Illnesses in the present gestation; Fetal malformation; Childbirth complications	Questionnaire	Descriptive analysis Frequency analysis
Intervention assessment data	Satisfaction with the assistance given	Questionnaire	Descriptive analysis Frequency analysis
	Perception level regarding anxiety, stress, depression and port-partum depression	Edinburgh Postpartum Depression Scale Depression Anxiety Stress Scale-21	Descriptive analysis Frequency analysis
	Perception level regarding signals (symptoms and feelings) of bereavement	Perinatal Grief Scale	Descriptive analysis Frequency analysis
	Difficulties with life routine resumption	Perinatal Grief Scale	Descriptive analysis Frequency analysis

#### Bias (*Table****3***)

**Table 3 Tab3:** Possible Issues and Solutions

	Possible Biases	Possible Solutions
1	Health care professionals may disregard important orientations or may have difficulties in changing their routine in the beginning	The Reference Professional will guide them from the beginning of the project and so on
2	A mistake regarding gestational age or baby weight on the maternity ward reports may include/exclude a woman from the sample	The information regarding the baby (birth, death) will be checked with the mother in the first contact
3	Mistakes made while filling out the documents created by this project	The Reference Professional will help filling out the documents and will follow up the case discussions
4	The mother/family does not authorize collection of some items listed in the project (picture, for instance)	The Reference Professional and the Bereavement Professional will manage this situation and consider alternatives to solve this matter. If necessary, researchers will assist them
5	During interview, a woman from the pre-intervention group reports that she has received care based on the supportive guidelines regarding perinatal bereavement	During the first contact, she will be asked for some information that may help avoid this bias

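### Care received is checked only in the pre-intervention group, at the eligibility contact; if women are left out because of it, the before/after contrast overstates the effect of implementation

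*Protocol article*

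**What the plan says.** The protocol article (Abstract, Method) defines the intervention as the implementation of the guidelines and compares 20 women before it with 20 after it.

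- **The bias named.** Table 3, row 5, in the Bias section describes the case where "a woman from the pre-intervention group reports that she has received care based on the supportive guidelines regarding perinatal bereavement". It concerns the pre-intervention group only.
- **The remedy.** "During the first contact, she will be asked for some information that may help avoid this bias". No consequence for the woman is stated.
- **What first contact is for.** Research instruments and data sources says "The researcher will contact each candidate to verify eligibility for this study, inviting them to participate and scheduling a meeting". The Pre-intervention section gives the same order: criteria are checked first, and the invitation and interview follow.
- **Eligibility.** "Women *exclusion criteria* are to not understand Portuguese and have severe mental health impairment". The inclusion criteria cover residence, period, gestational age, birth weight and time of death. None concerns care received.
- **Selection.** "The first 20 women from each group who accept to take part in this study will be interviewed".
- **The premise.** "It is estimated that women who had a baby born in the pre-intervention group did not receive a care based on the supportive guidelines".
- **Incomplete delivery after implementation.** Row 1 of Table 3 foresees that "Health care professionals may disregard important orientations or may have difficulties in changing their routine in the beginning" and answers this with guidance to staff. It does not screen women.

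**The concern.** Asking a woman about her care does not change the care she had. A question at the eligibility contact can keep such a report out of the interview only if the answer affects whether she is interviewed. Row 5 therefore reads most naturally as a screen, applied to one group and resting on the woman's own account.

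The study asks what implementation changes in these four wards. That needs care before implementation as it actually was, good cases included. A pre group cleared of those cases is a worse comparator than the real one, and the intervention looks better against it. Because the first 20 who accept are taken, a woman left out would be replaced by the next, and the final count of 20 would not show that a screen had been used.

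The screen would also select on something the study sets out to measure. The Objectives include assessing the care received at the two time points, and the Descriptive analysis section reports how often harms arose from care that did not follow the guidelines.

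**Working it through.** **No plan figure to reproduce.** The sample size is pragmatic (20 + 20 = 40). The protocol gives no effect size, uptake rate or rate of prior guideline-type care.

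**Effect on the contrast.** Let
- d = effect of the care on a woman who receives it (not given);
- a = share of post-intervention women who receive it (not given; row 1 suggests it may be below 1);
- f = share of pre-intervention women who receive it (presumed to be about 0; no rate given).

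Assume that d is the same for all women, that receipt of care is unrelated to prognosis, and that the screen removes every pre-group woman who received such care. Expected contrasts are then:
- no screen in either group: (a − f)d, the effect of implementation;
- screen in the pre group only: a·d;
- screen in both groups: d.

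The pre-only screen adds a·d − (a − f)d = f·d. The ratio to the unscreened contrast is a/(a − f):

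| a (assumed) | f = 0 | f = 0.1 | f = 0.2 | f = 0.3 |
|---|---|---|---|---|
| 1.0 | 1.00 | 1.11 | 1.25 | 1.43 |
| 0.8 | 1.00 | 1.14 | 1.33 | 1.60 |
| 0.7 | 1.00 | 1.17 | 1.40 | 1.75 |

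For example, 0.8/(0.8 − 0.1) = 1.14 and 0.7/(0.7 − 0.3) = 1.75.

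**Direction of the post-group part.** Removing post-intervention women who received no such care would raise the contrast from a·d to d. Keeping them therefore lowers it.

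**Effect on harm frequencies.** Let h1 be the frequency of a Safety Thermometer harm among pre-group women who had guideline-type care, and h0 the frequency among the rest. Without a screen the pre-group frequency is f·h1 + (1 − f)h0. With the screen it is h0. The rise is f(h0 − h1). The ten items are drawn from the guidelines themselves, so h0 should exceed h1, and the rise occurs whether or not the care affects mental health.

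**If receipt of care goes with prognosis.** Suppose d = 0 but women who received such care would score 0.5 SD better anyway (assumed). The screen alone then creates a false difference of 0.5f: 0.025 SD at f = 0.05 and 0.15 SD at f = 0.3. With 20 per group the standard error is √(2/20) = 0.316 SD, and the two-sided type I error rises from 5% to about 5.1% and 7.6% respectively.

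**Scale.** With an assumed two-sided 5% level, 20 per group has 80% power for a difference of (1.960 + 0.842) × 0.316 = 0.89 SD.

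**The case against.** The strongest reply is that no exclusion is written. Row 5 says only that information will be asked for, and the listed exclusion criteria are language and severe mental health impairment. That is correct, so exclusion is an inference here. It does not clear the plan, because row 5 then either adds an unlisted criterion or leaves the decision to whoever makes the contact.

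A second reply is that row 5 may be aimed at contamination. The Preparation phase is described before the pre-intervention phase and already includes awareness work and the writing of operating procedures. A woman listed as pre might therefore have been cared for under the project itself. This is plausible, and checking for it would be legitimate, but a date rule does that job directly without using the woman's account of her care.

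A third reply is that the protocol presumes no prior exposure, and its Rationale section says Brazil has had no such guidelines. At f = 0 there is no bias. Yet the same section says professionals act on their own beliefs, so care varies, and row 5 would serve no purpose if exposure could not occur.

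Two stronger readings are tempting and are not supported. A reader might infer that keeping post-intervention women who received no guideline care also inflates the effect. It dilutes the effect, and a comparison of periods needs those women. A reader might also infer that any pre-group woman who saw or held her baby would be removed. Row 5 refers only to care based on the guidelines and does not say which elements would count.

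It is also true that care received is already to be recorded by questionnaire and related to the scales. That makes the fix easy, but it cannot recover women who were never interviewed.

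**Conclusion.** The point holds conditionally. The documents establish a check on care received in one group only, placed where eligibility is decided, with no stated consequence and no matching criterion. If the check keeps women out, the contrast for implementation is biased upward by f·d and pre-group harm frequencies rise by construction.

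The documents do not give the size. The ratios of 1.11 to 1.75 rest on assumed values of a from 0.7 to 1.0 and f from 0.1 to 0.3, and the ratio is 1.00 at f = 0. The upward bias is relative to the effect of implementation. Relative to d, the effect of care actually received, a·d is still no larger than the truth.

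Severity is moderate. The harm depends on an unstated exclusion and on some prior exposure, and in the prognostic illustration the false difference is small beside what 20 per group can detect. It still bears on who enters the sample and should be settled before recruitment.

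**What to change.** Replace the row 5 solution with a statement that:

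1. women are assigned to groups by the date of the loss relative to the start of the intervention in their ward;
2. no eligible woman in either group is excluded because of the care she reports;
3. care received is recorded identically in both groups, with the existing questionnaire and the ten Safety Thermometer items, and used to describe how far care overlapped between periods;
4. the main comparison is by period, and any as-received comparison is a sensitivity analysis only.

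No mirror screen should be added to the post-intervention group. The cost is one table row and one line in the recruitment script, with no new data collection. The downside is that the observed difference may be smaller than with a screened pre group.
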